## Abstract

**Background:**

Intramuscular injections of botulinum toxin A (BoNT-A) have been a cornerstone in the treatment of spasticity for the last 20 years. In Norway, the treatment is now offered to two out of three children with spastic cerebral palsy (CP). However, despite its common use, the evidence for its functional effects is limited and inconclusive. The objective of this study is to determine whether BoNT-A makes walking easier in children with CP. We hypothesize that injections with BoNT-A in the calf muscles will reduce energy cost during walking, improve walking capacity, increase habitual physical activity, reduce pain and improve self-perceived performance and satisfaction.

**Methods/design:**

This randomized, double-blinded, placebo-controlled, multicenter trial is conducted in a clinical setting involving three health regions in Norway. Ninety-six children with spastic CP, referred for single-level injections with BoNT-A in the calf muscles, will be invited to participate. Those who are enrolled will be randomized to receive either injections with BoNT-A (Botox®) or 0.9% saline in the calf muscles. Stratification according to age and study center will be made. The allocation ratio will be 1:1. Main inclusion criteria are (1) age 4 − 17.5 years, (2) Gross Motor Function Classification System levels I and II, (3) no BoNT-A injections in the lower limbs during the past 6 months and (4) no orthopedic surgery to the lower limbs during the past 2 years. The outcome measures will be made at baseline and 4, 12 (primary endpoint) and 24 weeks after injections. Primary outcome is change in energy cost during walking. Secondary outcomes are change in walking capacity, change in activity, perceived change in performance and satisfaction in mobility tasks, and pain. The primary analysis will use a linear mixed model to test for difference in change in the outcome measures between the groups. The study is approved by the Regional Ethical Committee and The Norwegian Medicines Agency. Recruitment started in September 2015.

**Discussion:**

The evaluation of effect is comprehensive and includes objective standardized tests and measures on both impairment and activity level. Results are to be expected by spring 2019.

**Trial registration:**

ClinicalTrials.gov, NCT02546999. Registered on 9 September 2015.

**Electronic supplementary material:**

The online version of this article (doi:10.1186/s13063-016-1772-8) contains supplementary material, which is available to authorized users.

## Background

Cerebral palsy (CP) is the most common cause of neurological disability in childhood, and the motor signs associated with the condition include primary neuromuscular deficits, such as spasticity, muscle weakness, and decreased selective motor control, and secondary musculoskeletal problems such as bony malformations and contractures [1].

Impaired walking is a main clinical feature of CP, and although approximately 70% of children with CP are able to walk, they all experience varying degrees of restrictions related to this function [2]. Such restrictions include reduced walking speed [3], impaired balance [4] and high energy costs (ECs) during walking [5]. The ECs during walking increase with increasing level of disability [6] and age [7], and these impairments may, therefore, in part contribute to fatigue; a common complaint in children and youths with CP [8]. Moreover, recurrent musculoskeletal pain is common, affecting both general activity and walking [9, 10]. As a consequence, children with CP are in general less active than their peers, and they less often take part in social activities [11].

The dominating motor disorder in CP is spasticity, defined as a velocity-dependent increase in resistance to passive movement [12], present in more than 80% of the children [2]. The introduction of intramuscular injections of botulinum toxin A (BoNT-A) in the 1990s represented a significant breakthrough in the treatment of spasticity. BoNT-A is a neuromuscular paralyzing agent and it results in a dose-dependent chemo-denervation of the muscle by inhibiting the release of the neurotransmitter acetylcholine at the neuromuscular junction. Currently, treatment with BoNT-A is offered to as many as two thirds of all children with spastic CP and more than half of the children are able to walk independently [13].

Among children able to walk, a main goal of this treatment is to improve gait [14], and thereby improving the potential for higher levels of activity and participation. It is well-documented that BoNT-A reduces spasticity [15, 16]; however, despite being commonly used, evidence for functional effects is limited and inconclusive [17, 18]. In a systematic review [19], including eight randomized control trials (RCTs) the effects on walking were specifically addressed. The authors found that five of the eight studies were of low methodological quality, and seven got low scores on clinical relevance. The main limitations of the included studies related to differences in outcome measures, lack of a-priori defined effect sizes, and variations in follow-up time. The authors of the systematic review, therefore, had to rely on their “general impression” of improvement in “any functional outcome.” Based on this “general impression” the authors concluded that the use of BoNT-A with usual care or physiotherapy seemed to improve walking of children with CP emphasizing that their conclusions should be appraised carefully owing to the limited quality of included trials. Other long-term follow-up studies, taking a pragmatic approach in order to reflect clinical practice, were unable to document cumulative or persistent benefit on walking of repeated BoNT-A injections [20]. Thus, a fair summary of the existing medical literature is that the evidence for an effect of BoNT-A injections in the leg muscles on walking is limited and inconclusive.

The main objective of the current trial is, therefore, to investigate whether injections of BoNT-A in the calf muscles (m. gastrocnemius and m. soleus) make walking easier in children and adolescents with CP within a time span of 6 months, as judged by reduced EC during walking. Secondary objectives are to explore whether injections of BoNT-A increase activity, improve walking capacity, decrease musculoskeletal pain, and improve perceived performance and satisfaction related to mobility tasks.

We hypothesize that injections of BoNT-A in the calf muscles will reduce EC during walking, improve walking capacity, increase habitual physical activity and reduce pain. Moreover, we hypothesize that injections with BoNT-A will improve perceived performance and satisfaction related to ambulation. Secondary, we hypothesize that younger children and children with lower gross motor function will improve more in EC than older children and children with greater gross motor function.

In a substudy of this RCT, we aim to identify different CP phenotypes of responders to BoNT-A treatment and, moreover, to gain insight into the processes underlying BoNT-A-induced changes in walking. On that account, we want to identify gait and muscle activation patterns, spasticity and strength characteristics related to the response of BoNT-A on our primary and secondary outcome measures. Moreover, semistructured qualitative interviews will be conducted on a subset of participants (minimum 25) and their parents. Details of these studies are not presented in this paper.

## Methods/design

### Study design and setting

The WE-Study is designed as an industry-independent, double-blinded, placebo-controlled, superiority trial where participants are randomized to receive either injections of BoNT-A or saline (placebo) in the calf muscles. The allocation ratio will be 1:1. It is a multicenter study conducted in a clinical setting, involving three out of four health regions in Norway as well as the Norwegian University of Science and Technology, NTNU. The study will be conducted according to the Declaration of Helsinki and ICH-Good Clinical Practice guidelines. The study protocol follows the SPIRIT 2013 (Standard Protocol Items: Recommendations for Interventional Trials) guidelines [21]. The SPIRIT Checklist (Additional file 1) and figure (Table 1) are provided.

**Table 1 Tab1:** Standard Protocol Items: Recommendations for Interventional Trials (SPIRIT) figure

Study period						
	Enrolment	Allocation	Post allocation			Close-out
Time point	Baseline		Intervention	P1 4 weeks post	P2 12 weeks post	P3 24 weeks post
Enrollment:						
Eligibility screen	x					
Informed consent	x					
Allocation		x				
Interventions:						
Saline			x			
Botulinum toxin A			x			
Assessments:						
Energy cost	x			x	x	x
Habitual physical activity	x			x	x	x
Pain	x			x	x	x
Perceived change in performance and satisfaction	x			x	x	x
Spasticity test	x			x	x	x
Passive range of motion in the ankle	x			x	x	x

Monitoring will be carried out according to a predefined plan, independent of the sponsor and with no competing interests. Protocol modifications will be reviewed by the Regional Ethics Committee (REC). Substantial modifications will also be reviewed by The Norwegian Medicines Agency. Processing of personal study data will be done according to procedures approved by the data protection official at each study center. The trial registration data are provided in Table 2.

**Table 2 Tab2:** Trial registration data

Data category	Information
Primary registry	ClinicalTrials.gov NCT02546999
	EudraCT Number 2014-002539-32
Secondary identifying numbers	REC North 2013/1195
	The Norwegian Medicines Agency 14/15799-9
Sponsor	St. Olav’s University Hospital, Trondheim, Norway
Contact	[contact]
Short title	The WE-Study (Walking Easier with cerebral palsy)
Scientific title	Does botulinum toxin A make walking easier in children with cerebral palsy?
Country of recruitment	Norway
Population	Children with cerebral palsy (4 − 17.5 years)
Intervention	Active comparator: botulinum toxin A (Botox®)
	Placebo comparator: saline
Study type	Interventional parallel-group, randomized, double-blinded
	Phase IV
	Primary purpose: treatment effect
First enrollment	September 2015
Target sample size	96
Primary outcome	Energy cost during walking
Secondary outcome	Activity, pain, walking capacity, perceived benefit

### Participants

Eligible to participate are children and adolescents between 4 and 17.5 years of age (at the time of inclusion) with spastic unilateral or bilateral CP. The gross motor function of the participants should be at levels I or II according to the Gross Motor Function Classification System (GMFCS) [22] and they should not have been treated with BoNT-A in the lower limbs during the past 6 months or have undergone orthopedic surgery to the lower limbs in the last 2 years prior to study participation. Moreover, participants must be able to take verbal instructions. Exclusions are made based on the following criteria: history of prior adverse reactions to BoNT-A, presence of infection at the proposed injection site(s), subclinical or clinical evidence of defective neuromuscular transmission or other underlying neurological disorders that may be affected by BoNT-A injections, use of aminoglycoside antibiotics or spectinomycin, or other medicinal products that interfere with neuromuscular transmission (e.g., neuromuscular blocking agents), women with childbearing potential not using contraception, pregnant or breastfeeding women, children needing deep sedation, or any other reason in the opinion of the investigator. Children who receive concurrent injections in the upper limbs may be included in the study. Each study center will have one person in the study team responsible for introducing eligible participants to the study and the information given will be both orally and written. The same person will be responsible for obtaining written consent before baseline testing.

Once enrolled in the study, every reasonable effort will be made to avoid dropout and there will be close communication with participants and caregivers in the follow-up period. Patients may be discontinued from study treatment and assessments at any time. Specific reasons for discontinuing a patient for this study are: voluntary discontinuation by the patient, safety reason as judged by the principal investigator, major protocol deviation, incorrect enrollment, i.e., the patient does not meet the required inclusion/exclusion criteria for the study, deterioration in the patient’s condition which, in the opinion of the principal investigator, warrants study discontinuation (to be recorded as an adverse event; AE) and patient noncompliance to study treatment and/or procedures. Reason for discontinuation will be recorded in the web-based Case Report Form (eCRF) used in the study, and the participant will be offered an assessment including both primary and secondary outcomes before leaving the trial. After completing the study period, the participants will continue their regular follow-up at the hospital. Insurance coverage for this study is made through membership of the Drug Liability Association.

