### Study visits

Flow of participants and the timeline is presented in Fig. 1. The primary endpoint will be 12 weeks post injection, when a clinical effect can be expected. Outcomes at 4 and 24 weeks post injection will also be evaluated in order to control for the specific paralyzing effect on the muscle [27] and a possible delayed functional effect [15], respectively. Thus, the outcome measures will be assessed at baseline and 4, 12 and 24 weeks after injections (Fig. 1: P1, P2 and P3).

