### Statistical analysis

The statistical analysis for the primary aim will be performed using a LMM including data from baseline and 4, 12 and 24 weeks post intervention. The test for difference in change in the primary outcome measure from baseline to 12 weeks between the treated and placebo group will be done using a post-hoc test following the LMM. Age, GMFCS level, number of prior BoNT-A treatments and study center will be considered as potential covariates. A similar model will also be used to study the secondary outcome measures. The LMM handles missing data for the outcome measure. Nonparametric tests will be used to test for a between-group difference in change score for secondary outcome measures expressed with ordinal data, and for scalar data in case the requirements for the parametric tests are not met. The effect size will be expressed as mean difference between the groups in change from baseline to 12 weeks with a 95% confidence interval.

In addition to investigating the independent effect of BoNT-A on walking, the associations between the change scores of the primary and secondary outcome measures will also be studied.

The level of significance is set to 0.05 and no formal adjustments for multiple testing will be carried out.

A complete plan for the analyses of the outcome measures will be made before unmasking group adherence. Results will be reported according to the Consolidated Standards of Reporting Trials (CONSORT) Statement [39].

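### The discontinuation rule lets investigators end outcome assessments, not only treatment, so injected children can lose the 12-week primary value for reasons other than withdrawn consent

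*Protocol article*

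**What the plan says.** The Participants section of the protocol article sets one discontinuation rule for treatment and follow-up together: "Patients may be discontinued from study treatment and assessments at any time". Besides voluntary withdrawal and safety, the listed reasons include "major protocol deviation, incorrect enrollment, i.e., the patient does not meet the required inclusion/exclusion criteria for the study". A worsening clinical course is a further reason, worded as "deterioration in the patient’s condition which, in the opinion of the principal investigator, warrants study discontinuation". Poor compliance is another: "patient noncompliance to study treatment and/or procedures".

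Two provisions soften the rule. The section opens with a commitment that "every reasonable effort will be made to avoid dropout", and for a child who is discontinued, "the participant will be offered an assessment including both primary and secondary outcomes before leaving the trial".

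Table 1 shows a single intervention point after allocation. The Study visits section then states that "the outcome measures will be assessed at baseline and 4, 12 and 24 weeks after injections", with week 12 as the primary endpoint. On gaps in the data, the Statistical analysis section says: "The LMM handles missing data for the outcome measure".

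**The concern.** In a trial with continuing medication, a discontinuation rule usually serves to stop the drug. Here the drug is given once. After the injections no study treatment remains to be stopped, so the rule can act only on outcome collection. A child who breaks a protocol requirement, proves ineligible, complies poorly or gets worse may then have no 12-week energy-cost value, although the family has not withdrawn.

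Two things are at stake. The first is bias. Removal for deterioration is tied to how the child is doing, and removal for deviation or noncompliance may be. If the toxin works, more placebo children than treated children would be expected to worsen, and the observed difference would be too small. The second is information. Removals that could be avoided use up part of the 30% dropout allowance in Sample size and power. A later analysis plan can choose how to handle missing values, but it cannot recover a measurement that was never made.

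**Working it through.** **1. What the rule does at each stage.**
- Between allocation and injection: it can stop treatment and assessments.
- After injection: no treatment is left, so it stops assessments only.
- At exit: one assessment is offered, at whatever time the child leaves. It stands in for the 12-week value only if it happens to fall there.

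**2. How the listed reasons relate to outcome.**
- Deterioration: directly related.
- Major deviation and noncompliance: possibly related; the text does not say.
- Incorrect enrolment: eligibility is fixed before randomisation, so removal is not outcome-related in itself. It costs numbers and completeness of follow-up as randomised.

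**3. The plan's own figures.** Inputs from Sample size and power: difference in change 0.684 J/kg/m, SD of change 1.0, two-sided 5% level, power 80%, dropout 30%.
- Normal approximation: n = 2 × (1.960 + 0.842)² / 0.684² = 33.55 per group. Dividing by 0.70 gives 47.9, so 48 per group and 96 in total, as stated.
- The stated 32 per group before dropout is slightly below this (34 after rounding up; 35 with the exact t test). The present point does not depend on that gap.
- Power (t test) is 91% if all 48 per group have a 12-week value and 79% at 33.6 per group, which is 48 × 0.70.

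**4. Illustrative bias, before any recovery by the model.** The removal rates are assumptions, because the documents give none. Take 12-week change as Normal(0, 1) on placebo and Normal(−0.684, 1) on active. Positive values mean worsening. Remove every child above one cut-off c, the same in both arms. Each arm's mean falls by φ(z)/Φ(z), with z = c on placebo and z = c + 0.684 on active.

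| Placebo removed | c | Active removed | Placebo mean falls by | Active mean falls by | Net shrinkage | Share of 0.684 |
|---|---|---|---|---|---|---|
| 5% | 1.645 | 1.0% | 0.1031/0.95 = 0.109 | 0.0265/0.990 = 0.027 | 0.082 | 12% |
| 10% | 1.282 | 2.5% | 0.1755/0.90 = 0.195 | 0.0578/0.975 = 0.059 | 0.136 | 20% |

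The observed difference would be about −0.60 or −0.55 instead of −0.684. With no true effect, both arms lose the same tail and the net bias is zero.

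**5. What a mixed model could recover.** A simulation used the same distributions, with a week-4 value correlated 0.5 or 0.7 with week 12. Children above a worsening of 0.5 were removed with probability one half (15% of placebo, 6% of active). The 12-week mean was adjusted by regression on week 4, which approximates what the mixed model does.
- Removal driven by the observed week-4 value: estimate −0.68, so essentially no bias.
- Removal driven by the unseen week-12 value: −0.605 (correlation 0.5) or −0.630 (correlation 0.7). The shrinkage is 0.079/0.684 = 12% or 0.054/0.684 = 8%. Without the adjustment the estimate was −0.58.

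The model therefore repairs removal that recorded data explain, and only part of the rest.

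**The case against.** The best defence is that the rule is permissive and surrounded by safeguards. Children may be discontinued; they need not be. The section commits to avoiding dropout. Deterioration counts only when the principal investigator judges that it warrants leaving the study. Participants and those treating and assessing them are blinded, so deliberate removal by arm is unlikely. Deterioration that prompts removal has by definition been noticed and may be captured at a visit or at the exit assessment, in which case missing at random is tenable. The 30% allowance exists for losses of this kind.

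Much of this stands and limits the size of the problem. It does not remove it. Blinding does not prevent unequal removal if the treatment works. The exit assessment is optional and untimed. The rule also works against the protocol's own retention commitment.

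A reader might infer several stronger things that the documents do not support:
- That removal is automatic. The wording only permits it.
- That only injected children are affected. Table 1 places allocation before intervention, so a child can leave in between.
- That every listed reason produces outcome-related missing data. Incorrect enrolment does not in itself.
- That these children are excluded from analysis, so that the randomised comparison is broken. Nothing in the text discards data already collected, and the model uses baseline, 4-, 12- and 24-week values.
- That the bias is 16–29% of the target. Those figures (0.109/0.684 and 0.195/0.684) come from trimming the worst 5–10% of one arm and none of the other, which a blinded rule gives no reason to expect.

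Stating the missing-at-random assumption and adding sensitivity analyses normally belong in the statistical analysis plan. That plan is not shown, and their absence here is not a fault.

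**Conclusion.** The point holds as a should-fix. The protocol article permits investigators to end assessments for deviation, incorrect enrolment, deterioration or noncompliance. After a single injection session, the only effect of doing so is to lose later outcomes, including the primary one.

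The size cannot be derived from the documents, because no removal rate is given. On the assumption that 5–10% of placebo children are removed at a cut-off common to both arms, and that the target effect is true, the difference shrinks by about 0.08–0.14 J/kg/m (12–20% of 0.684) before any recovery by the model. In the separate simulation of an adjustment for week 4, shrinkage was 8–12% when removal depended on unseen values and about zero when it depended on observed ones. With no true effect and the same rule in both arms, bias is about zero. Under this mechanism the risk is therefore an understated benefit and lost power, not a false claim of superiority.

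**What to change.** In the Participants section, separate stopping study treatment from stopping study assessments. Limit the latter to withdrawal of consent or assent, or a safety concern with the assessment itself. State that all other randomised children keep the 4-, 12- and 24-week assessments and are analysed in their allocated group, whatever the deviation, eligibility error, compliance or clinical course. The exit assessment can remain for families who do withdraw.

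The cost is a short protocol amendment; the visits are already scheduled. A few ineligible or non-compliant children stay in the analysis and may dilute the effect slightly. Decisions on clinical care are unchanged. The amendment is useful only while children are still in follow-up, because missed visits cannot be recovered.

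### Children who stop before week 12 leave assessment with only an exit test, so no 12-week energy-cost value is planned for them

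*Protocol article*

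**What the plan says.** All references are to the protocol article.

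- **Participants, scope of stopping.** "Patients may be discontinued from study treatment and assessments at any time". Stopping therefore covers outcome measurement, not only treatment.
- **Participants, reasons.** Besides voluntary withdrawal, the list includes safety, major protocol deviation, incorrect enrolment, deterioration and "patient noncompliance to study treatment and/or procedures". Several of these are decided by the investigator and do not imply that the family refuses further visits.
- **Participants, what the leaver is offered.** "the participant will be offered an assessment including both primary and secondary outcomes before leaving the trial". The section names no scheduled visit for this assessment and does not provide for a 12-week assessment after stopping.
- **Treatment procedure, Study visits and Table 1.** There is one intervention time point, and follow-up is counted from it. Week 12 is the primary endpoint, chosen because a clinical effect can be expected by then. Week 4 is measured for a different purpose: "in order to control for the specific paralyzing effect on the muscle".
- **Statistical analysis.** The primary model is a "LMM including data from baseline and 4, 12 and 24 weeks post intervention". The primary comparison is "The test for difference in change in the primary outcome measure from baseline to 12 weeks between the treated and placebo group". On missing values the section says: "The LMM handles missing data for the outcome measure".

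**The concern.** After the injections there is no continuing study drug to stop. A child who is discontinued at week 6, for example for noncompliance with procedures, could still be measured at week 12, and that value would belong in a comparison of the groups as randomised. The Participants section instead ends assessment at departure and ties the last test to the departure date.

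Two things are at stake. The first is validity. A linear mixed model fitted to the available visits gives an unbiased 12-week contrast only if, given the data already observed, the missing 12-week values resemble those that were seen. Deterioration is a listed reason for stopping, and a child who leaves for that reason may well be heading for a worse 12-week value than the earlier ones predict. The second is precision, because each missing 12-week value weakens the primary test.

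This is a rule of conduct, not of analysis. A later analysis plan can say how an exit value is used, but it cannot supply a 12-week measurement that was never taken.

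**Working it through.** **Inputs.** From Primary outcome measure and Sample size and power: difference 0.684 J/kg/m (10% of 6.84), SD of change 1.0, two-sided 5% level, 80% power, 32 per group, 30% dropout, 48 per group (96 in total).

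**Step 1: the plan's own figure.**
- Normal approximation: n = 2 × (1.960 + 0.842)² × 1.0² / 0.684² = 2 × 7.85 / 0.468 ≈ 33.6, so 34 per group. The exact t test gives 34.5, so 35.
- The stated 32 is close but slightly low. Its exact t-test power is 76.8%.
- Dropout: 32 / 0.7 = 45.7, so 46; 34 / 0.7 = 48.6, so 49. The stated 48 lies between them.

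**Step 2: expected leavers.** 48 × 0.30 = 14.4, about 14 per arm, leaving 48 − 14 = 34.

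**Step 3: power by number of 12-week values per arm.** Exact two-sided t test with noncentrality 0.684 × √(n/2):

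| Case, if all 14 leavers stop before week 12 | 12-week values per arm | Noncentrality | Power |
|---|---|---|---|
| No 12-week visit for leavers | 34 | 2.82 | 79.4% |
| 4 of 14 attend at week 12 | 34 + 4 = 38 | 2.98 | 83.7% |
| 7 of 14 attend at week 12 | 34 + 7 = 41 | 3.10 | 86.4% |

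The gain is 4 to 7 percentage points.

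**Step 4: sensitivity to the time of leaving.** Follow-up runs to week 24, and the 30% is an overall allowance. If half the leavers (7 per arm) stop after week 12, 34 + 7 = 41 per arm already have the primary value and power is 86.4% with no change. Recovering 2 or 3 of the other 7 gives 43 or 44 per arm and 88.0% or 88.7%, a gain of about 2 points.

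**Assumptions.** The number who attend (4 or 7) and the share who leave before week 12 are not in the documents. The table also supposes that recovered children show the same difference and SD as completers, and it counts 12-week values only. The mixed model draws some information from earlier visits, so the true gain in precision would be somewhat smaller.

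**What cannot be computed.** The possible bias from values not missing at random has no figure here. It would need the reasons for leaving by arm and the unobserved outcomes.

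**The case against.** **The exit assessment is a reasonable provision.** It carries no date, so a site could place it at the next scheduled visit, and the same section promises efforts to prevent dropout. For a family that wants to leave, a test now may be more realistic than a return weeks later. This stands as a real trade-off. It does not answer the case of a child removed by the investigator, whose family may be willing to return, and nothing in the section directs sites to aim for week 12.

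**The sample size already allows for this loss.** That is correct: with 34 per arm, power is about 79%, close to the planned 80%. The trial is not underpowered because of this rule. The allowance protects precision, however, not the missing-at-random assumption.

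**A mixed model uses incomplete records.** This is also correct. A child with a baseline and a week-4 value, or an exit value, still informs the 12-week estimate under missing at random. What remains is that the assumption carries the weight for these children.

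**A stronger reading is tempting.** A reader might infer that an exit value taken between visits must be either thrown away or filed as the 12-week value, diluting the treatment effect. The article does not say so. It states no carry-forward or visit-window rule. An exit value could be placed at the nearest visit or modelled at its actual time. Such a rule commonly belongs in the analysis plan, which the article defers: "A complete plan for the analyses of the outcome measures will be made before unmasking group adherence". Its absence here is no finding, and no loss of power from misfiled values can be claimed.

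**Conclusion.** The point holds in a limited form. The protocol ends outcome assessment when a child is discontinued, although a single injection session leaves no reason in the design to do so. It provides an assessment tied to departure and not to the primary endpoint. For children who stop before week 12, the primary result then depends on missing at random, which is questionable where deterioration is the reason.

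The gain available from a change is modest: power of 84–86% against about 79% if all 14 leavers per arm stop before week 12 and 4 to 7 of them attend, and about 2 points if half leave later. These figures rest on assumed attendance and timing. The stronger case for the change is that it reduces reliance on an assumption that the data cannot test. The rule does not invalidate the primary analysis. It is a low-cost improvement.

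**What to change.** In Participants, add to the sentence on the exit assessment: a child who stops before week 12 is asked, if the family is willing, to attend the scheduled 12-week visit for the primary outcome, and for the secondary outcomes if willing. The assessment before leaving is offered when the family declines, and it is recorded in the eCRF under its actual date.

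This changes only when outcomes are measured. It does not touch the reasons for discontinuation or any clinical decision, and it leaves the family free to refuse.

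**Cost.** One sentence in the protocol and an unscheduled-visit page in the eCRF, with no added test per child. The downside is that some families who agree to week 12 may not return, so a few exit tests that would have been obtained at departure could be lost.
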